### Randomization and Blinding

A computer-generated random number sequence with variable block sizes will be used to allocate participants in a 1:1:1 ratio. Randomization will be stratified by gender and primary presenting concern (depression vs anxiety) to ensure balanced group allocation on these prognostically important variables. The allocation sequence will be concealed from research staff responsible for recruitment. Because of the nature of the intervention, participants and session facilitators cannot be blinded. Outcome data will be collected primarily through self-report instruments administered through a secure platform, and analyses will be conducted on deidentified group codes until the primary models are finalized.

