### Sample Size Calculation

An a priori power analysis was conducted using G*Power. On the basis of meta-analyses of related VR-based mental health interventions [30,31], a medium effect size (f=0.25) was assumed. To achieve 80% power at an alpha level of .05 for the primary group-by-time comparison, a required sample of 90 participants was indicated. To account for an anticipated attrition rate of 20% to 30%, consistent with rates reported in VR intervention literature, the recruitment target is set at 110 participants. A sensitivity analysis indicates that with 30% attrition (leaving approximately 77 participants), statistical power for the primary comparison would be reduced to approximately 70%, which is acknowledged as a limitation. To minimize attrition, the study will implement flexible scheduling, session reminders, brief mid-study check-ins, and graduated VR exposure in the first session to identify and manage cybersickness early. If observed attrition exceeds 30%, this will be reported transparently and considered in the interpretation of results. This sample size determination was made for the primary clinical outcomes and was not specifically powered for mediation or moderation analyses; those analyses will therefore be treated as exploratory.

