### Safety Monitoring and Adverse Events

Adverse events will be monitored throughout the trial. Participants will be asked about dizziness, nausea, eyestrain, disorientation, social distress, and symptom worsening at each VR session and at formal assessment points. The Simulator Sickness Questionnaire (SSQ) will be administered at the end of every VR session to track habituation trajectories and detect differential cybersickness across groups; SSQ scores will be examined as a potential covariate in sensitivity analyses. Sessions may be paused or discontinued if participants experience clinically meaningful discomfort. All adverse events and withdrawals will be recorded.

Predefined clinical thresholds will be used to identify participants requiring immediate attention. A BDI-II total score exceeding 28 (indicating severe depression) or any endorsement of suicidal ideation on BDI-II item 9 (score ≥1) at any assessment point will trigger immediate clinical review. Similarly, a BAI total score exceeding 25 (indicating severe anxiety) will prompt review. Self-report assessments will be scored in real time at each formal assessment point, with automatic flagging of scores exceeding these thresholds. Session facilitators will also conduct a brief verbal check-in before and after each VR session to monitor participant well-being.

When a clinical threshold is met, the session facilitator will immediately notify the principal investigator, who will conduct or arrange a clinical risk assessment within 24 hours. Participants meeting clinical concern criteria will be referred to the psychological counseling center at Hunan Traditional Chinese Medical College for nonurgent concerns or to the psychiatric emergency department at the nearest affiliated hospital for acute crises. The principal investigator ([name]) will serve as the designated safety officer responsible for overseeing all safety monitoring procedures and referral decisions. Participants who are referred for clinical care may continue in the trial if deemed safe by the assessing clinician or may be withdrawn if continued participation poses a risk to their well-being.

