### Data Management

All data will be entered into a secure electronic database with verification procedures. Identifiable information will be stored separately from outcome data on encrypted institutional servers, accessible only to authorized members of the research team.

For the primary outcomes, linear mixed-effects models will be used to examine group, time, and group×time effects on BDI-II and BAI scores. Separate models will be fitted for depression and anxiety outcomes, with participant-level random intercepts to account for repeated measures over time. Gender and primary presenting concern (the stratification variables) will be included as covariates, and baseline symptom severity will be considered in model specification as appropriate. The primary planned contrasts will compare the experimental group with the active control group at T1 and T2; comparisons involving the waitlist control group will be secondary and should be interpreted with caution, given the expectancy and novelty confounds inherent in waitlist comparisons. Post hoc pairwise comparisons will be adjusted for multiple testing using a Holm procedure. Secondary outcomes will be analyzed using analogous mixed-model approaches. Cybersickness (SSQ scores) will be examined as a potential covariate in sensitivity analyses to assess whether differential simulator sickness across groups confounds the primary results. Missing data assumptions will be examined, with maximum likelihood estimation in mixed models as the primary approach and multiple imputation and per-protocol analyses used as sensitivity analyses where appropriate. Exploratory analyses will examine whether changes in Basic Psychological Need Satisfaction Scale scores are associated with changes in BDI-II and BAI scores and whether music-movement synchronization moderates selected outcomes; these analyses will be interpreted as hypothesis generating rather than confirmatory causal tests.

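### As worded, the plan lets the baseline-severity term of the primary model be settled after outcomes have been analysed by coded group, and the codes hide direction but not significance

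*Protocol article*

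**What the plan says.** Three statements in the protocol article bear on this point.

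- **Order of work** (Randomization and Blinding): "analyses will be conducted on deidentified group codes until the primary models are finalized". The word 'until' places analysis by group code before the models are final.
- **What is fixed** (Data Management): "linear mixed-effects models will be used to examine group, time, and group×time effects on BDI-II and BAI scores". The same paragraph sets separate models for depression and anxiety, a participant-level random intercept, the two stratification variables as covariates, and maximum likelihood estimation. It also sets the contrasts: "The primary planned contrasts will compare the experimental group with the active control group at T1 and T2".
- **What is open** (Data Management): "baseline symptom severity will be considered in model specification as appropriate". The article does not say whether baseline severity is a covariate, part of the repeated response, or subtracted as a change score.

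Nothing in the article says that the primary models are settled before by-group outcome results are available.

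**The concern.** Coding the arms is meant to keep the analyst's choices independent of the result. For that it must hide whatever the analyst could select on. With a two-sided test of two arms, the labels carry only the sign. The size of the difference, the interval width and the p-value can all be read from coded data. An analyst who still has to decide how baseline enters could therefore see which version makes the two VR arms differ significantly, without knowing which arm is which.

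This matters because the primary outcomes are self-reported in a trial where participants and facilitators are unblinded, which the Discussion acknowledges as a limitation. A model choice that could have been informed by results would be a second, avoidable reason to doubt a positive finding.

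**Working it through.** The plan states no figure on this point, so there is none to reproduce. Two things can be checked: whether the codes mask significance, and how much the open term could matter.

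**Inputs**

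- Alpha 0.05, from Sample Size Calculation: "To achieve 80% power at an alpha level of .05 for the primary group-by-time comparison". Sidedness is not stated; two-sided is assumed.
- Participants per arm: the plan will "allocate participants in a 1:1:1 ratio", so 110/3 ≈ 37 randomized per arm. The same section considers a case "with 30% attrition (leaving approximately 77 participants", so 77/3 ≈ 26 per arm.
- T0–T1 correlation ρ: not in the document. The range 0.3 to 0.7 is assumed.

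**Check 1: label swap.** A simulated data set with three arms, three visits and 110 participants was fitted with a random-intercept mixed model. It was then refitted with the two VR codes exchanged.

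| Contrast | Estimate, codes as given | Estimate, codes swapped | p, both ways |
|---|---|---|---|
| T1 | −0.8417 | +0.8417 | 0.595083 |
| T2 | −4.0343 | +4.0343 | 0.010851 |

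Only the sign moves.

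**Check 2: keeping the smaller of two p-values.** Let X be the T0 score and Y the T1 score, both with unit variance, and let d denote the difference in means between the VR arms. With no true effect:

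- change from baseline: dY − dX, with variance proportional to 2(1 − ρ)
- baseline-adjusted: dY − ρ·dX, with variance proportional to 1 − ρ²
- covariance between them: 1 − ρ − ρ² + ρ = 1 − ρ²
- correlation between them: √[(1 − ρ²)/(2(1 − ρ))] = √[(1 + ρ)/2]

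The chance that at least one is significant is 1 − P(|Z₁| < 1.96 and |Z₂| < 1.96) for two standard normal variables with that correlation. The simulated column is from 20,000 null two-arm trials per setting.

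| ρ | √[(1 + ρ)/2] | Large-sample result | Simulated, n = 26 / 37 per arm |
|---|---|---|---|
| 0.3 | 0.806 | 7.8% | 7.7% / 7.5% |
| 0.5 | 0.866 | 7.3% | 7.2% / 7.0% |
| 0.7 | 0.922 | 6.8% | 6.9% / 6.7% |

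In the same runs each specification, fixed in advance, rejected in 4.7% to 5.2%.

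**Check 3: a third option.** If an unadjusted comparison of T1 levels is also allowed, the smallest of three p-values falls below 0.05 in about 9% to 10% of null trials over the same range.

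**Check 4: direction.** With two specifications, false positives that favour the experimental arm rise from 2.5% to about 3.3% to 3.8%.

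**The case against.** The strongest reply is that the sentence may describe ordinary blinded analysis: prespecified models are fitted and checked under codes, and the codes are then broken. A separate statistical analysis plan may also lock the models earlier. Both are possible. But the plain wording puts finalization after coded analysis, and the same article leaves a model term open. An earlier lock elsewhere would conflict with this sentence, which would still need correcting.

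Several stronger readings might be inferred, and the document does not support them.

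- **That the primary model as a whole is open.** It is not. The model family, random intercept, stratification covariates and contrast arms are all fixed; the gap shown here is the baseline term.
- **That coding is the trial's one protection against bias.** The article also describes concealed and stratified allocation, a matched active comparator, a familiarization session, intention-to-treat analysis and prospective registration. None of these governs the timing of model choice, but the codes do not stand alone.
- **That the codes do nothing.** They hide which VR arm is favoured, so they block selection on direction.
- **That the waitlist code is obvious.** The Safety Monitoring section says "The Simulator Sickness Questionnaire (SSQ) will be administered at the end of every VR session", and the waitlist arm has no intervention sessions during the trial. But this reveals the code only if session or in-VR data are linked to the coded outcome file when models are chosen, which the article does not say.
- **That the error rate is 9% to 10%.** This needs the T1-level comparison as a third option. The wording of the planned contrasts could be read that way, but it fits poorly with a primary outcome defined as change and a sample size set for a group-by-time comparison.

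**Conclusion.** The concern holds in limited form. The stated order of work allows one open term, the handling of baseline severity, to be settled with coded by-group results in view. The codes do not hide significance from whoever settles it.

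The possible cost is a type I error of about 7% to 8% instead of 5% for one outcome at one time point, or about 10% at most if a T1-level contrast is also admitted. These figures rest on a two-sided test, 26 to 37 per VR arm, an assumed T0–T1 correlation of 0.3 to 0.7, and deliberate choice of the smallest p-value. They come from a simplified two-arm, single-time-point setting, not the full three-visit model. They bound what the wording permits and do not predict how the team will behave. The change is worth making because the exposure is real, bounded and easy to remove.

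**What to change.** Make two linked edits.

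1. In Data Management, replace the open clause with one named specification for baseline severity. The T0 score should be either part of the repeated response or a covariate for T1 and T2, not both.
2. In Randomization and Blinding, replace the clause on group codes with wording such as: *The primary models, including the baseline term, covariates and contrasts, are locked and dated before any post-baseline outcome is analysed by group, coded or not. Any earlier model checks use data pooled over arms. Group codes are kept as an additional safeguard.*

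The cost is two sentences and a dated sign-off, with no change to participants, data collection or sample size. According to the Results section, no participants had been enrolled as of April 2026, so the change can precede all data. The downside is that a model problem found after the lock must be reported as a labelled deviation or sensitivity analysis.

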### Safety Monitoring and Adverse Events

Adverse events will be monitored throughout the trial. Participants will be asked about dizziness, nausea, eyestrain, disorientation, social distress, and symptom worsening at each VR session and at formal assessment points. The Simulator Sickness Questionnaire (SSQ) will be administered at the end of every VR session to track habituation trajectories and detect differential cybersickness across groups; SSQ scores will be examined as a potential covariate in sensitivity analyses. Sessions may be paused or discontinued if participants experience clinically meaningful discomfort. All adverse events and withdrawals will be recorded.

Predefined clinical thresholds will be used to identify participants requiring immediate attention. A BDI-II total score exceeding 28 (indicating severe depression) or any endorsement of suicidal ideation on BDI-II item 9 (score ≥1) at any assessment point will trigger immediate clinical review. Similarly, a BAI total score exceeding 25 (indicating severe anxiety) will prompt review. Self-report assessments will be scored in real time at each formal assessment point, with automatic flagging of scores exceeding these thresholds. Session facilitators will also conduct a brief verbal check-in before and after each VR session to monitor participant well-being.

When a clinical threshold is met, the session facilitator will immediately notify the principal investigator, who will conduct or arrange a clinical risk assessment within 24 hours. Participants meeting clinical concern criteria will be referred to the psychological counseling center at Hunan Traditional Chinese Medical College for nonurgent concerns or to the psychiatric emergency department at the nearest affiliated hospital for acute crises. The principal investigator ([name]) will serve as the designated safety officer responsible for overseeing all safety monitoring procedures and referral decisions. Participants who are referred for clinical care may continue in the trial if deemed safe by the assessing clinician or may be withdrawn if continued participation poses a risk to their well-being.

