**Conclusions:**

This protocol describes a self-determination theory–informed, multicomponent VR intervention designed to evaluate whether adding a bundled social layer to a matched solo exergame improves short-term mental health outcomes. The trial is expected to provide initial evidence on efficacy, safety, and potential mechanisms while generating hypotheses for future dismantling and longer-term trials.

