### Interventions

#### Experimental Group: VR Social Musical Exergame

Participants in this arm will engage in the VR intervention twice a week for 45 minutes over 6 weeks. Prior to the first intervention session, all participants in VR conditions (experimental group and active control group) will complete a 15-minute familiarization session using a neutral, nontherapeutic VR environment to reduce initial novelty effects and identify individuals who may experience significant cybersickness. Waitlist control participants will receive a brief (5-minute) VR demonstration to partially equalize technology exposure. The experimental condition is conceptualized as a bundled social VR musical exergame designed to support autonomy, competence, and relatedness simultaneously.

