#### Active Control Group: VR Solo Musical Exergame

This group will engage in a VR exergame with the same frequency, duration, exercise intensity, game content, and music design as the experimental group. However, all social features will be disabled. This condition is designed to preserve autonomy and competence support while removing the bundled social layer, and it serves as the primary comparator for testing the unique contribution of social interaction.

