#### Waitlist Control Group

Participants in this group will receive a standardized digital handbook on mental health. They will be instructed to maintain their usual activities for the 6-week study period. To address ethical considerations, this group will be offered access to the VR intervention after the trial. Comparisons with this group are intended as secondary estimates of effects relative to minimal guidance rather than as the primary test of the social mechanism.

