##### Music-Movement Synchronization

Music-movement synchronization is an objective behavioral metric captured by the VR software, reflecting the accuracy and timing of participants’ physical movements relative to musical beats. Within the SDT framework, this variable is treated as an exploratory behavioral indicator that may reflect task engagement and perceived competence. It is not a primary or confirmatory outcome; any associations with other variables will be interpreted as hypothesis generating.

All self-report and fitness measures will be collected at T0, T1, and T2. In-VR behavioral data will be captured continuously during the intervention period.

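### Harm questions are put about 14 times after randomization in the VR arms and about twice in the waitlist, so any tabulation of solicited adverse events for VR versus waitlist would be inflated in the VR arms

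*Protocol article*

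**What the plan says.** Safety Monitoring and Adverse Events sets the occasions on which harms are solicited: "Participants will be asked about dizziness, nausea, eyestrain, disorientation, social distress, and symptom worsening at each VR session and at formal assessment points". The same section attaches two further checks to VR sessions: the SSQ at the end of each one, and a facilitator's verbal check-in before and after.

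The Interventions section fixes how many sessions each arm has:

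- Social VR: "Participants in this arm will engage in the VR intervention twice a week for 45 minutes over 6 weeks".
- Solo VR: "This group will engage in a VR exergame with the same frequency, duration, exercise intensity, game content, and music design as the experimental group".
- Waitlist: a digital handbook and no sessions. "They will be instructed to maintain their usual activities for the 6-week study period". Its only VR contact is a short demonstration: "Waitlist control participants will receive a brief (5-minute) VR demonstration to partially equalize technology exposure".

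Formal assessments are common to all arms: "All self-report and fitness measures will be collected at T0, T1, and T2". BDI-II and BAI threshold flagging takes place at these assessments.

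On purpose, the Abstract's Conclusions say: "The trial is expected to provide initial evidence on efficacy, safety, and potential mechanisms". The safety section says adverse events are monitored for the duration of the trial and that all are recorded. It does not say how they will be compared between arms. Study Design makes social versus solo VR the primary comparison and waitlist comparisons secondary.

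**The concern.** The number of times a participant is asked about harms depends on the assigned arm. Four of the six solicited items (dizziness, nausea, eyestrain, disorientation) are largely about VR exposure, and asking about them at sessions is natural. The other two, social distress and symptom worsening, can occur in any arm, and worsening matters especially in a sample selected for depression or anxiety. For those two items the waitlist is the only non-VR reference for the background rate, and it has no stated harm question between baseline and week 6, apart from the demonstration if that counts.

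If solicited events were tabulated by arm, the VR arms could show more events than the waitlist with no true difference in risk. This is a data-collection rule fixed in the protocol. An analysis plan can restrict a comparison to common time points, but it cannot recover reports that were never asked for.

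**Working it through.** The documents give no event rate and no figure on this point, so there is nothing to reproduce. The counts come from the text; the probabilities below are assumptions.

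**Number of askings after randomization**

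- Sessions per VR arm: 2 per week × 6 weeks = 12.
- Formal assessments after randomization: T1 and T2 = 2.
- Each VR arm: 12 + 2 = 14. Waitlist: 2, or 3 if the demonstration is treated as a session.
- Up to and including T1: 13 versus 1.
- Social versus solo VR: 14 versus 14, so the schedule creates no difference.

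**Upper end: no recall of earlier events at T1**

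Let p be an assumed chance of a positive answer per asking, equal in every arm and independent across askings. The share with at least one report after k askings is 1 − (1 − p)^k.

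| p (assumed) | VR, k = 14 | Waitlist, k = 2 | Ratio |
|---|---|---|---|
| 0.01 | 13.1% | 2.0% | 6.6 |
| 0.02 | 24.6% | 4.0% | 6.2 |
| 0.05 | 51.2% | 9.8% | 5.3 |
| 0.10 | 77.1% | 19.0% | 4.1 |

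Counting the demonstration (k = 3) at p = 0.02 gives 1 − 0.98³ = 5.9% and a ratio of 24.6/5.9 = 4.2. In expected number of positive answers rather than participants, the ratio is 14p to 2p, or 7:1.

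**Allowing for recall**

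A waitlist participant asked at T1 may report events from the preceding six weeks. Let r be the fraction of what the 12 sessions would have caught that is recalled at T1. The waitlist share becomes 1 − (1 − p)²(1 − rp)¹². At p = 0.02, with VR at 24.6%:

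| r (assumed) | Waitlist | Ratio |
|---|---|---|
| 0 | 4.0% | 6.2 |
| 0.25 | 9.6% | 2.6 |
| 0.5 | 14.9% | 1.7 |
| 1 | 24.6% | 1.0 |

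Full recall removes the artefact; anything less leaves some of it. Correlation between a participant's answers would also bring the participant-level ratio down.

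**After the fix**

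Counting only T1 and T2 reports gives k = 2 in every arm, so under equal true rates the ratio is 1.0 by construction.

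**The case against.** The strongest objection is that the document states no adverse-event comparison with the waitlist. The one between-group harm purpose it names is differential cybersickness by SSQ, which the Discussion describes as a matter of social versus solo VR. How events are tabulated by arm is commonly left to a fuller document. A reader might infer that the plan pools every recorded event across the three arms, or that its safety comparison is already biased. The text supports neither: it says events will be recorded, and it expects initial evidence on safety without promising a statement against the waitlist. This part of the objection stands, so the point is a risk to any such tabulation and not an error in a stated analysis.

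Four further arguments stand in part.

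- The primary comparison is untouched because both VR arms share one schedule. This stands in full.
- Worsening on the trial's own instruments is measured equally: BDI-II and BAI are taken at T0, T1 and T2 in all arms. It would therefore be too strong to say that worsening in the waitlist cannot be compared. These scores do not cover social distress, however, and may miss a transient worsening between visits.
- A sevenfold difference in askings need not mean a four- to sixfold difference in participants reporting. Those ratios assume no recall at T1 and are the top of the range.
- Nor can one say that waitlist harms go unseen for six weeks. Sample Size Calculation plans "brief mid-study check-ins" and does not confine them to the VR arms. They are presented as a way to limit attrition and their content is not given, so they may or may not include a harm question.

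**Conclusion.** The point holds within limits. The protocol fixes unequal solicitation of harms, about 14 askings against 2 (or 3), between each VR arm and the waitlist. Any tabulation of solicited events for VR versus waitlist that includes session reports would be inflated in the VR arms, and this matters most for symptom worsening and social distress. At an assumed 2% per asking the spurious ratio lies between about 1.0 and 6.2. It rests on three assumptions that the documents do not settle: the per-asking probability, independence of answers, and recall at T1.

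Social versus solo VR is not affected, and BDI-II/BAI scores and flags are symmetric across all arms. Severity is minor to moderate, because waitlist comparisons are secondary. It is still worth settling before enrollment, because the trial expects to report on safety and unsolicited waitlist reports cannot be collected afterwards.

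**What to change.** Three changes:

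1. State that any adverse-event comparison including the waitlist uses only events solicited at T1 and T2, with the same questions and look-back period in all three arms, supplemented by worsening on BDI-II and BAI.
2. State that session-collected events and SSQ scores are reported for the two VR arms only.
3. Put the same symptom-worsening and social-distress questions to all three arms at the mid-study check-ins already planned under Sample Size Calculation, and say that the waitlist takes part in them.

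The cost is a few sentences and one short question set at an existing contact. The three-arm table will contain fewer events, but the session data remain available in full for the VR arms. The Results section reports that no participant had been enrolled as of April 2026, so on that status the change affects no collected data.

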##### Cardiorespiratory Fitness

Cardiorespiratory fitness will be estimated using the Young Men’s Christian Association 3-minute step test, a practical field-based measure with established validity [45,46]. This outcome is treated as a secondary health-related outcome rather than as a primary mechanistic SDT variable.

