The protocol also has important limitations that should be considered when interpreting future results. First, the 1-month follow-up captures only short-term stability rather than long-term remission; it cannot assess relapse patterns, sustained behavioral change, or long-term clinical trajectories, and future trials should include follow-up periods of at least 3 to 6 months. Second, the social condition is a bundled manipulation that combines voice chat, collaboration, competition, and visible performance comparison; therefore, the trial cannot isolate the independent effect of each social feature, and the study should be understood as a preliminary multicomponent efficacy trial that may inform future dismantling or factorial designs to identify active therapeutic ingredients. Third, the primary outcomes (BDI-II and BAI) are self-report measures administered in an unblinded trial, which increases susceptibility to expectancy, demand characteristics, and placebo effects, particularly given the immersive and novel nature of the VR intervention; future trials should consider incorporating clinician-administered measures (eg, the Hamilton Depression Rating Scale) or objective biomarkers alongside self-report instruments. Fourth, although the intervention is informed by SDT, the bundled design does not isolate or manipulate autonomy, competence, and relatedness independently; any associations between need satisfaction and symptom change are therefore exploratory and cannot establish causal mediation. Fifth, differential cybersickness between the social and solo VR conditions could confound group comparisons, as more complex social interactions may elicit different levels of simulator sickness. Sixth, the study is powered for the primary clinical outcomes but not specifically for mediation or moderation analyses, which are therefore exploratory and hypothesis generating. Finally, although the eligibility range has been narrowed to 18 to 25 years to reduce developmental heterogeneity, individual differences within this developmental period may still influence intervention response.

If the intervention demonstrates favorable short-term effects and acceptable safety, the findings may support a scalable and engaging digital mental health approach that is feasible on consumer-grade VR hardware. The protocol may also inform future dismantling studies that test specific social features, as well as trials with longer follow-up and broader multisite implementation.

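### Falls, injuries and exertional symptoms are not among the harms participants are asked about in this exercise trial, so they may be under-counted relative to the harms that are prompted

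*Protocol article*

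**What the plan says.** The relevant text is in the Protocol article, Safety Monitoring and Adverse Events. It opens broadly: "Adverse events will be monitored throughout the trial". It then sets the prompted content: "Participants will be asked about dizziness, nausea, eyestrain, disorientation, social distress, and symptom worsening at each VR session and at formal assessment points". The one structured safety instrument follows: "The Simulator Sickness Questionnaire (SSQ) will be administered at the end of every VR session", with the stated purpose of tracking and comparing cybersickness.

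The same section has three general provisions that are not tied to the list:

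- "Sessions may be paused or discontinued if participants experience clinically meaningful discomfort"
- "Session facilitators will also conduct a brief verbal check-in before and after each VR session to monitor participant well-being"
- "All adverse events and withdrawals will be recorded"

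On exposure, the Interventions section gives both VR arms two 45-minute sessions a week for 6 weeks, at the same exercise intensity; the social arm adds collaborative or competitive team tasks. Under Cardiorespiratory Fitness, the trial uses a "3-minute step test, a practical field-based measure with established validity". The outcomes section schedules fitness measures at T0, T1 and T2 and exempts no arm.

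On what will be claimed, the Abstract's conclusions expect the trial to yield first evidence on safety, and the Discussion reasons from a condition: "If the intervention demonstrates favorable short-term effects and acceptable safety".

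**The concern.** The prompted list does not match the intervention. Of the six items, four are symptoms typical of cybersickness and two are psychological or social. None asks about a fall or collision, a strain or other injury, chest symptoms or breathlessness. Those are the harms one would expect from moving to a beat with a headset on, and from a step test.

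A harm asked about at every session and a harm recorded only when it happens to come up are not measured on the same scale. If both are equally frequent, the prompted one will look more common. A reader of the safety table could then conclude that the exergame's harms are mainly cybersickness, when part of that pattern comes from how the data were collected. Harms that were not asked about cannot be reliably recovered afterwards.

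A smaller point concerns the waitlist arm. The open check-in is attached to VR sessions, so waitlist participants, who also do the step test, have no stated equivalent. The chance that an unlisted harm comes to light may therefore differ between the VR arms and the waitlist.

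**Working it through.** The plan gives no figure for harms, so there is none to reproduce. The check compares what is prompted with what participants do, and then illustrates the size.

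**1. Prompted content against exposure**

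| Type of harm | Asked directly? | Other route in the plan |
|---|---|---|
| Cybersickness | Yes: four of the six items, plus the SSQ | Check-in, general recording |
| Psychological or social | Yes: two of the six items, plus scored questionnaires | Check-in, general recording |
| Fall or collision | No | Observation, check-in (VR sessions only), volunteered report |
| Musculoskeletal pain or injury | No | Same |
| Exertional symptoms | Only where they appear as dizziness or nausea | Same |

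**2. Planned exposure**

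- Sessions per VR participant: 2 per week × 6 weeks = 12.
- VR participants: 110 × 2/3 = 73.3, about 73.
- VR sessions at full attendance: 73.3 × 12 = 880. If only the 77 participants left at the plan's 30% attrition are counted: 77 × 2/3 × 12 = 616.
- Step tests, at most: 110 × 3 = 330.

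**3. Effect of incomplete capture**

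Let p be the true risk per participant and c the share of affected participants whose harm is recorded. Neither is in the documents; both are assumed, and a range is shown. With n = 73, expected recorded cases = n·p·c, and the chance of recording at least one = 1 − (1 − p·c)^n.

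| p | c = 100% | c = 50% | c = 25% |
|---|---|---|---|
| 2% | 1.5 cases; 77% | 0.7; 52% | 0.4; 31% |
| 5% | 3.7 cases; 98% | 1.8; 84% | 0.9; 60% |
| 10% | 7.3 cases; >99% | 3.7; 98% | 1.8; 84% |

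If a prompted and an unprompted harm have the same true risk and the prompted one is fully captured, the ratio of their recorded rates is simply c.

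**4. What a zero would mean**

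With no recorded case among 73, the one-sided 95% upper limit for p·c is 1 − 0.05^(1/73) = 4.0%. At full capture this is the limit for p itself. At c = 50% it becomes 4.0%/0.5 = 8.0%, and at c = 25% it becomes 4.0%/0.25 = 16%. Because c is unknown, the limit on the true risk is unknown too.

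**5. Comparing the social and solo arms**

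At p = 5% and full capture, each arm of about 37 expects 37 × 0.05 = 1.9 cases. Even a split of 5 against 0 gives a two-sided Fisher p of 2 × C(37,5)/C(74,5) = 2 × 435,897/16,108,764 = 0.054. The trial could not establish an arm difference in injuries at this risk, whether or not they are prompted.

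**The case against.** The strongest reply is that the plan does not confine adverse events to the six items. Monitoring runs throughout, every adverse event is to be recorded, sessions can be halted for discomfort of any kind, and facilitators check in before and after each VR session. In a facilitated session a fall or collision is likely to be seen. This stands: the issue is possible under-counting, and these harms are not left unrecorded. It does not remove the point. A rule to record events says what happens once an event is known and not how it comes to be known; a general question about well-being is a weaker prompt than a named item; and the check-in does not extend to the waitlist.

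A second reply is that a journal article leaves the adverse-event form to the full protocol. That would be decisive if the article were silent. It is not: it gives the list, its timing and the instrument. The full form may be longer, in which case the change is already made and only the article needs correcting.

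Three stronger readings might be inferred, and the documents support none of them:

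- *That no physical harm is asked about.* Dizziness, nausea, eyestrain and disorientation are physical symptoms, and the first two can come from exertion. The gap is narrower: falls or collisions, injury, and other exertional symptoms.
- *That a difference in physical harm between social and solo play would be missed because of the list.* Both VR arms are followed in the same way, nothing in the text shows differential ascertainment between them, and step 5 shows that the numbers are too small in any case.
- *That the exclusion criteria conflict with the exercise content.* The clause on contraindications to VR participation is open-ended and can cover the exergame, no two places contradict each other, and pre-exercise screening is a detail that an article may leave to the full protocol.

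**Conclusion.** The point holds in a limited form. As written, active questioning targets cybersickness and psychological or social harm, while falls or collisions, musculoskeletal injury and most exertional symptoms depend on unprompted reporting. Their recorded rates may be too low in absolute terms and relative to the prompted harms.

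The size cannot be derived from the documents. On an assumed 5% true risk in 73 VR participants, recorded cases fall from 3.7 at full capture to 1.8 at half capture and 0.9 at a quarter, while the chance of recording at least one remains 84% and 60% respectively. These figures rest on assumed risk and capture, on all 73 being followed, and on participants being independent.

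A reader might infer that acceptable safety could not be concluded at all. That goes too far: events that come to light are recorded, and the article promises only first evidence and speaks of acceptable safety conditionally. The proper conclusion is that the safety statement would be less reliable for these harms than for the prompted ones. No primary outcome, estimate or test is affected.

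**What to change.** Add three groups to the existing question list: falls or collisions, musculoskeletal pain or injury, and exertional symptoms. Ask about them at each VR session and at T0, T1 and T2 after the step test, with identical wording in all arms, waitlist included. The exact items, and any clinical response to them, are for the trial's clinicians.

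If the list is left as it is, state with the safety results that these harms were collected by unprompted report only and that their rates should not be set beside those of the prompted harms.

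The cost is a few more questions on a form already in use and a small protocol amendment, with no added visits. The article gives the trial as not yet recruiting in April 2026, with recruitment expected from May 2026, so the change is best made before the first participant is enrolled.
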